## Abstract

**Background:**

Alcohol use is an important issue among problem drug users. Although screening and brief intervention (SBI) are effective in reducing problem alcohol use in primary care, no research has examined this issue among problem drug users.

**Objective:**

The objective of this study is to determine if a complex intervention including SBI for problem alcohol use among problem drug users is feasible and acceptable in practice. This study also aims to evaluate the effectiveness of the intervention in reducing the proportion of patients with problem alcohol use.

**Methods:**

Psychosocial intervention for alcohol use among problem drug users (PINTA) is a pilot feasibility study of a complex intervention comprising SBI for problem alcohol use among problem drug users with cluster randomization at the level of general practice, integrated qualitative process evaluation, and involving general practices in two socioeconomically deprived regions.
Practices (N=16) will be eligible to participate if they are registered to prescribe methadone and/or at least 10 patients of the practice are currently receiving addiction treatment. Patient must meet the following inclusion criteria to participate in this study: 18 years of age or older, receiving addiction treatment/care (eg, methadone), or known to be a problem drug user. This study is based on a complex intervention supporting SBI for problem alcohol use among problem drug users (experimental group) compared to an “assessment-only” control group. Control practices will be provided with a delayed intervention after follow-up. Primary outcomes of the study are feasibility and acceptability of the intervention to patients and practitioners. Secondary outcome includes the effectiveness of the intervention on care process (documented rates of SBI) and outcome (proportion of patients with problem alcohol use at the follow-up). A stratified random sampling method will be used to select general practices based on the level of training for providing addiction-related care and geographical area. In this study, general practitioners and practice staff, researchers, and trainers will not be blinded to treatment, but patients and remote randomizers will be unaware of the treatment.

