#### Phase 2: Exploratory Study

A pilot study in addiction clinics showed that SBIs are effective in reducing alcohol consumption among opiate-dependent patients [16]. There is a current proposal to establish the acceptability and effectiveness of the intervention by conducting a feasibility study in primary care.

This protocol reflects the development and piloting phases of the MRC’s “Framework for the design and evaluation of complex interventions to improve health” [20,22]. The present study will provide key parameters regarding the feasibility and acceptability of the intervention to patients and practitioners. As such, this research is essential to inform the design and conduct of a larger cluster randomized controlled trial (RCT).

The specific objectives of the study are as follows. First, this study aims to develop a complex intervention that will enhance SBI for problem alcohol use among problem drug users in primary care. This study will help to establish the practical feasibility and acceptability of complex intervention (1) by conducting a pilot study (with randomization at the level of practice), (2) exploring the feasibility and acceptability of the intervention under study and related research procedures to GPs, practice nurses, and patients, and (3) exploring the fidelity of the interventions as delivered in practice. Finally, we can decide to inform the subsequent design of a definitive cluster RCT by describing the optimum configuration of the complex intervention and by estimating the key parameters in such a trial (ie, practice/patient recruitment and retention rates, intraclass correlation coefficient for primary outcome measures, and the likely effect of intervention under study on these measures).

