##### Patient Measures

These measures include indirect examination and direct examination. At baseline and follow-up, the study battery will include the following: (1) Alcohol Use Disorders Identification Test (10 items) (AUDIT), (2) Maudsley Addiction Profile (MAP), and (3) Readiness Ruler.

AUDIT developed by the World Health Organization is used to identify a continuum of problem alcohol use [21,38].

MAP is a brief, structured questionnaire for treatment outcome research and measures problems specifically in four areas: substance use, health risk behavior, physical and psychological health, and personal/social functioning [18,39].

Readiness Ruler will assess patient’s motivational state regarding changing their drinking behavior [41].

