Effectiveness	Direct (interview at baseline and follow-up): AUDIT [38] Other drug use (eg, Maudsley Addiction Profile [39]) Motivation to change risky behavior (eg, Readiness ruler [40])		Indirect (review of clinical records): Results of chemical tests for alcohol and drugs (eg, breathalyzer or urine tests) will be also retrieved using the practice records to verify self-report measures

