### Data Analysis

Descriptive statistics will be estimated with respect to key feasibility variables. At baseline, rates of practice and patient recruitment, prevalence of problem drug use at participating practices, and baseline prevalence of problem alcohol use among problem drug users will be estimated. Process and fidelity evaluation of pilot educational intervention will be explored. Practice/patient retention rates, prevalence of problem alcohol use among problem drug users, and confounding factors such as practice busyness or person who performed SBI will be analyzed for outcome measures.

SPSS v20 and R software will be used for analysis by the HRB Center for Support and Training in Analysis and Research.

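### Every alcohol effect measure that the protocol defines is yes/no although the graded AUDIT is collected at both visits; reporting the score beside the proportion would make the treatment-effect estimate more precise at almost no cost

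*Protocol article*

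**What the plan says.** All references are to the protocol article.

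- **Abstract, Objective.** The effectiveness aim is to "evaluate the effectiveness of the intervention in reducing the proportion of patients with problem alcohol use".
- **Abstract, Methods.** The patient-level secondary outcome is "outcome (proportion of patients with problem alcohol use at the follow-up". The primary outcomes are feasibility and acceptability.
- **Data Analysis.** The follow-up quantities include "prevalence of problem alcohol use among problem drug users, and confounding factors such as practice busyness".
- **Power Calculations and Sample Size Estimates.** The pilot is not powered for effectiveness. The share of patients who cut down their drinking will be used to predict the size of the definitive trial.
- **Phase 2: Exploratory Study.** Parameters to be estimated for the definitive trial include the "intraclass correlation coefficient for primary outcome measures, and the likely effect of intervention under study on these measures".
- **Patient Measures.** The 10-item AUDIT is given at baseline and follow-up and "is used to identify a continuum of problem alcohol use".
- **Table 1, Effectiveness row.** AUDIT is listed with no cut-off: "Direct (interview at baseline and follow-up): AUDIT [38] Other drug use (eg, Maudsley Addiction Profile [39". The Readiness Ruler is listed there too.

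No section gives an AUDIT cut-off. None says how the AUDIT score will be summarised, and none gives a reason for working with proportions only.

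**The concern.** A yes/no version of a graded score treats unlike patients as alike. A patient whose score falls a long way but stays above the cut counts as unchanged, and a one-point move across the cut counts as full success. The effect estimate becomes less precise as a result.

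Precision is what this pilot needs, because it has few practices and one of its objectives is to estimate the likely effect for a definitive cluster trial. If only proportions are reported, the designers of that trial would also lack the SD of the AUDIT score, its correlation between the two visits and its ICC. They would need these to judge whether a score-based outcome allows a smaller trial.

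**Working it through.** **Inputs from the article.** 160 patients in 16 practices; 75% retention; 35% prevalence of problem alcohol use (national study of methadone patients in general practice). The intended 20% interview sample of 16 implies 80 intervention patients, hence equal arms.

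**Assumptions not in the article.** ICC of the score 0.01 to 0.10; equal cluster sizes; AUDIT is the score that is cut; illustrative follow-up proportions of 25%, 20% and 15%; for the skewness check, an AUDIT-like negative binomial distribution on 0 to 40 with a cut of 8.

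The 160 is justified by good-practice recommendations for pilots. It has no power or precision formula to reproduce, but its arithmetic is consistent: 16 × 10 = 160 and 0.20 × 80 = 16.

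**Step 1. Analysed sample.** 160 × 0.75 = 120, so 60 per arm and 120/16 = 7.5 per practice.

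**Step 2. Loss for a normal score and independent patients.** The relative efficiency of a cut at proportion p is φ(z_p)² / [p(1 − p)].
- At p = 0.35, z = −0.385 and φ = 0.3704.
- 0.3704² / (0.35 × 0.65) = 0.1372 / 0.2275 = 0.603.
- The loss is 39.7%. The standard error, relative to the effect, is 1/√0.603 = 1.29 times as large, and 1/0.603 = 1.66 times as many patients are needed.
- 120 patients then carry the information of about 120 × 0.603 = 72.

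The loss is 36% at p = 0.50 and 51% at p = 0.20.

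**Step 3. Clustering.** Cutting a score also lowers its ICC, so the two outcomes need separate design effects, 1 + (m − 1) × ICC. The adjusted efficiency is 0.603 × DE(score) / DE(binary).

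| Per practice | Score ICC | Binary ICC | DE score | DE binary | Efficiency | Loss |
|---|---|---|---|---|---|---|
| 7.5 | 0.01 | 0.006 | 1.065 | 1.039 | 0.618 | 38% |
| 7.5 | 0.05 | 0.030 | 1.325 | 1.197 | 0.668 | 33% |
| 7.5 | 0.10 | 0.061 | 1.650 | 1.395 | 0.713 | 29% |
| 10 | 0.10 | 0.061 | 1.900 | 1.547 | 0.740 | 26% |

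**Step 4. Skewness.** For the negative binomial scores (mean about 7, SD 5.4 to 8.8), the efficiency of the proportion against the raw mean is 0.642 to 0.677, a loss of 32% to 36%.

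**Step 5. What this means for the effect estimate.** With 60 per arm, 14 degrees of freedom (16 practices less 2 arms, t = 2.145), score ICC 0.05 and no true effect, the 95% half-width for the difference in proportions is 2.145 × √(2 × 0.2275/60 × 1.197) = 0.204, about 20 percentage points. It runs from 19 to 22 points over ICC 0.01 to 0.10.

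Power is used here only as a scale for precision (two-sided 5%, non-central t with 14 df, normal score without baseline adjustment, ICC 0.05):

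| Assumed change | d | Binary | Score |
|---|---|---|---|
| 35% to 25% | 0.29 | 18% | 25% |
| 35% to 20% | 0.46 | 36% | 52% |
| 35% to 15% | 0.65 | 60% | 82% |

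A harsher case was simulated with a skewed score, an effect only in baseline problem drinkers and a baseline-to-follow-up correlation of 0.6. When scores halve, power is 20% for the proportion (23% adjusted for baseline status), 30% for the raw score and 42% for the baseline-adjusted score. With a 30% fall the figures are 8%, 8%, 12% and 17%, so the gain is small when the effect is weak.

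**Step 6. Precision of the ICC.** The ANOVA estimator was simulated with 16 practices of 8 patients. The SD of the ICC estimate is 0.051 (score) against 0.050 (binary) at score ICC 0.01, 0.062 against 0.057 at 0.05, and 0.072 against 0.065 at 0.10. The cut does not worsen the absolute error. That error comes mainly from having only 16 practices.

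**The case against.** The strongest reply is that the article does not restrict the analysis to proportions. Table 1 lists AUDIT uncut under Effectiveness, with the Maudsley Addiction Profile and the Readiness Ruler. The Data Analysis section is a short descriptive list in a condensed article, and models or score summaries may sit in a fuller document. This stands in part. A reader might infer that the proportion with problem alcohol use is the only patient effectiveness outcome; Table 1 does not support that. What holds is narrower: each alcohol effect measure the article actually defines is yes/no, and that is a stated choice in the aim, the outcome and the sizing measure.

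A reader might also infer that the follow-up proportion in the Abstract supplies the effect and ICC for the definitive trial. The text does not say so. The Phase 2 section ties those parameters to the primary outcome measures, which the Abstract defines as feasibility and acceptability. The measure named for sizing is the proportion who reduce consumption, which concerns change and not follow-up status. It too is yes/no, so the concern carries over, but the link has to be made through the sample size section.

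Finally, the pilot is not powered for effectiveness and no decision rests on a significance test. That limits the weight of the power figures. It does not remove the point, because estimating the likely effect is a stated objective and its precision matters for that purpose.

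**Conclusion.** The point holds as an avoidable loss of precision on the treatment effect. At 35% prevalence the loss is about 40% under normality and independence, and roughly 26% to 38% once clustering (ICC 0.01 to 0.10, 7.5 to 10 patients per practice) or skewness is allowed for. These figures rest on AUDIT being the score that is cut, and on the assumed ICCs and score distributions.

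Two stronger readings are not supported. The 40% figure should not be quoted without its conditions. It would also be wrong to say that the cut makes the ICC estimate less precise, since its absolute error is about the same either way. What could be missing is the ICC of the score itself, if only proportions are reported.

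The outcome is secondary, and the raw AUDIT will be held for both visits, so nothing is lost beyond recovery. This is a worthwhile improvement and not a critical error.

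**What to change.** 1. In the Abstract outcomes and in Data Analysis, keep the proportion with problem alcohol use, so that the stated aim is still answered. Add beside it the between-arm difference in 3-month AUDIT score with a 95% CI, adjusted for baseline AUDIT and accounting for practice (a random effect or a cluster-level analysis).
2. Report the SD of the AUDIT score, its baseline-to-follow-up correlation and its ICC.
3. In Phase 2: Exploratory Study and in Power Calculations and Sample Size Estimates, state which alcohol measure supplies the effect and the ICC for the definitive trial, and include the AUDIT score among the parameters reported for it.

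The cost is some wording and one extra model, with no new data and no change to the design. A mean score difference is less directly clinical than a proportion, which is a reason to show both. AUDIT scores are likely to be skewed, so a bootstrap or transformed-scale sensitivity analysis should accompany the model.

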**Results:**

This study is ongoing and a protocol system is being developed for the study. This study may inform future research among the high-risk population of problem drug users by providing initial indications as to whether psychosocial interventions for problem alcohol use are feasible, acceptable, and also effective among problem drug users attending primary care.

**Conclusions:**

This is the first study to examine the feasibility and acceptability of complex intervention in primary care to enhance alcohol SBI among problem drug users. Results of this study will inform future research among this high-risk population and guide policy and service development locally and internationally.

## Introduction

### Overview

Problem alcohol use is associated with adverse health and economic outcomes, all the more so among problem drug users (eg, individuals currently using illicit drugs or trying to abstain from other illicit drugs such as benzodiazepines, cocaine, or heroin) [1,2]. Such alcohol use may decrease in response to psychosocial interventions whose benefits have been demonstrated in general adult populations. For example, a comprehensive review by Raistrick et al presented data on the effectiveness of many such interventions, including screening, further assessment, brief interventions, and alcohol-focused specialist treatment [3].

Primary care may have an important role in addressing problem alcohol use among problem drug users. Its potential impact on screening for alcohol problems and providing appropriate interventions in the general population has been described [4], although a recently published randomized trial indicates that more intensive primary-care-based interventions provide little by way of additional benefit to patient information alone [5]. Internationally, screening and brief interventions (SBI) are recommended as a treatment of choice for reducing alcohol use among problem drinkers in primary care [6,7], but these have not been tested in people who are addicted to other substances and who attend primary care [8]. It is important to address this issue because of the serious complications associated with problem alcohol use in this population, that is, the potential to increase the likelihood of a relapse to problem drug use, medical/psychological complications, liver disease, and so on [1,2].

Similar to other evidence-based interventions, the evidence on SBIs translates slowly into practice [9-11], and the findings from implementation studies are contradictory. For example, while a systematic review of interventions focused on increasing the use of SBI for hazardous alcohol consumption in primary care recommended complex, multicomponent strategies [12], a recent trial concluded that such a “tailored, multifaceted program aimed at improving general practitioner (GP) management of alcohol consumption” failed to show an effect and proved difficult to implement [13]. This also contradicts the conclusions of a recent paper, “real world evidence supports theory” of SBIs [14].

More impetus to this contradictory debate has been added by recent implementation studies and a controlled trial among problem drug users in secondary care that demonstrated feasibility of implementing SBIs among problem drug users in secondary care but suggested a controlled pilot study was necessary to establish key parameters for a similar evaluation in primary care [15-17]. The present study is designed to evaluate these issues.

### Previous Work in Ireland and Its Relation to Complex Intervention Theory

This protocol builds on our ongoing program of research that indicates (opiate) addiction treatment should also incorporate interventions that address problem use of alcohol and other illicit substances. For example, a national cross-sectional study reported that 35% of 196 patients attending GPs for methadone treatment also had problem alcohol use [18], while findings from a subsequent qualitative study highlight the need for a complex intervention to address this problem in primary care [19].

The UK Medical Research Council (MRC)’s “Framework for the Development and Evaluation of Complex Interventions for Randomized Controlled Trials (RCTs)” [20], which suggests following core phases to the development of complex health service interventions, informed the development of the intervention under study.

#### Preclinical Phase: Theory and Problem Identification

A national prevalence study showed problem alcohol use among patients attending general practice for methadone maintenance was high (35%) [18]. A review of scientific evidence found no studies examining this issue in primary care, but research in secondary or community care settings suggests that this type of intervention can be effective among problem drug users [21].

#### Phase 1: Modeling

The development of the complex intervention and clinical guidelines is informed by Cochrane Systematic review, qualitative interviews with health care providers and patients, and clinical guidelines.

Cochrane Systematic review was used to assess “psychosocial interventions for problem alcohol use in illicit drug users” [8]. Qualitative interviews with health care providers and patients that showed that barriers to implementation of alcohol intervention for drug users in primary care include patient factors, health care professional factors, and structural issues. The implementation strategies should utilize educational and support systems [19]. Clinical guidelines—informed by the findings of qualitative interviews, expert opinion through a Delphi-facilitated expert consensus process, and a Cochrane Systematic Review [8]—advocate SBI for problem alcohol use among problem drug users.

#### Phase 2: Exploratory Study

A pilot study in addiction clinics showed that SBIs are effective in reducing alcohol consumption among opiate-dependent patients [16]. There is a current proposal to establish the acceptability and effectiveness of the intervention by conducting a feasibility study in primary care.

This protocol reflects the development and piloting phases of the MRC’s “Framework for the design and evaluation of complex interventions to improve health” [20,22]. The present study will provide key parameters regarding the feasibility and acceptability of the intervention to patients and practitioners. As such, this research is essential to inform the design and conduct of a larger cluster randomized controlled trial (RCT).

The specific objectives of the study are as follows. First, this study aims to develop a complex intervention that will enhance SBI for problem alcohol use among problem drug users in primary care. This study will help to establish the practical feasibility and acceptability of complex intervention (1) by conducting a pilot study (with randomization at the level of practice), (2) exploring the feasibility and acceptability of the intervention under study and related research procedures to GPs, practice nurses, and patients, and (3) exploring the fidelity of the interventions as delivered in practice. Finally, we can decide to inform the subsequent design of a definitive cluster RCT by describing the optimum configuration of the complex intervention and by estimating the key parameters in such a trial (ie, practice/patient recruitment and retention rates, intraclass correlation coefficient for primary outcome measures, and the likely effect of intervention under study on these measures).

## Methods

### Overview of Study Design

Psychosocial intervention for alcohol use among problem drug users (PINTA) is a pilot feasibility study of a complex intervention to promote SBI for problem alcohol use among problem drug users, with cluster randomization at the level of general practice, and integrated qualitative process evaluation, involving general practice in two regions.

### Study Population

#### Recruitment and Random Selection of Practices

The following practices will be invited to participate, given written information on the study and their interest in participating:

All practices in two regions—Health Services Executive (HSE) Midwest and Dublin Mid-Leinster regionsAll practices that have been involved in previous related research with our group [18,23-29]General practices in the study regions that are affiliated with two of the Ireland’s six medical schools [30,31]

Practices will be eligible to participate if they are registered to prescribe methadone and/or have at least 10 patients currently receiving addiction-related care.

Of those who confirm their *interest* in the study and who are eligible to participate, a stratified random sampling technique will be used to select 16 practices.

Sampled GPs will be contacted about their participation, given further information on the study (eg, what their involvement will entail) and consulted about patient recruitment. The research team will telephone those not replying. Each practice will be visited by the principal investigator or lead researcher and provided with the information about the research program.

To ensure comparability between intervention and control groups for key practice characteristics, a restricted allocation involving stratified approach to randomization will be adopted. Prior to randomization, GPs who express their interest in participating will be grouped according to the level of training in providing addiction-related care (level 1 and 2), geographical location (Dublin/Midwest), with 16 randomly selected GPs using an independent remote randomization service.

To prescribe methadone, GPs are subject to clinical audit and must complete special training, while GPs providing methadone treatment for 15 or more patients are subject to more regular audit and advanced training. GPs who prescribe methadone for less than 15 patients are referred to as “level 1 GPs,” and those prescribing for 15 or more as “level 2 GPs.” Initiation of methadone therapy, treatment of patients with more complex medical and psychosocial needs (including alcohol dependence), and unstable drug use are only permitted by specialist addiction treatment services or by “level 2 GPs.” A more complex, difficult cohort of patients is attended by level 2 GPs and this might have implications for the success of the intervention. Therefore, it will be introduced in the data analysis as a potential confounder.

